## Background

Oncology researchers have identified muscle mass as a priority biomarker for cancer research [1]. There is compelling evidence that muscle quantity and function increases morbidity and mortality after a diagnosis of cancer, including both cancer-specific and overall mortality, risk of non-cancer comorbid conditions, and functional decline [2–7]. Low muscle size (area) is highly prevalent in patients diagnosed with cancer: prior studies of nonmetastatic breast and colorectal cancer patients have found 30% and 42% breast and colorectal cancer patients have low muscle size at diagnosis [8]. Muscle likely influences cancer-related outcomes through multiple physiologic, metabolic and functional pathways [9]. Proposed mechanisms include the important contribution of skeletal muscle in metabolism and systemic inflammation: skeletal muscle is the largest organ in the body and secretes cytokines and other peptides (known as myokines) that have autocrine, paracrine, or endocrine actions [10]. Muscle size also influences the pharmacokinetics of chemotherapy and is associated with dose-limiting toxicity [11], thereby reducing the effectiveness of these life-saving cancer therapies among individuals with low muscle mass.

After diagnosis, several factors increase the risk of muscle loss among cancer survivors, including direct effects of treatment on protein synthesis and degradation, alterations in nutrient intake due to nausea, and changes in energy expenditure due to inactivity or bedrest [12]. Despite growing knowledge of the importance of muscle mass at diagnosis in cancer patients, little is known about longer-term changes in muscle mass in cancer survivors. This manuscript describes a study protocol for a project that will measure muscle mass in female cancer survivors. In this project, we will use an innovate approach to measure muscle mass remotely, via the D3-Creatine (D_3_Cr) method. The overall aim of this project is to add to our understand of the antecedents and consequences of muscle mass in cancer survivors.

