## Materials and methods

### Study population

The [name] study (**M**u**s**cle mass in the **Li**fe and **L**ongevity **A**fter **C**ancer cohort) will include approximately 6000 postmenopausal women. Participants will be recruited from the ongoing Women’s Health Initiative (WHI) study cohort. The WHI is a prospective longitudinal study focused on examining causes of morbidity and mortality in postmenopausal women.

All [name] participants have been active participants in the WHI study since the 1990s. Postmenopausal women aged 50–79 years enrolled in the WHI clinical trials and observational study between 1993 and 1998 at 40 clinical centers across the U.S. (n = 161,808) [26]. Over the past thirty years, follow-up has been consistent and is still ongoing. In the initial phase of the WHI (up to 2005), participants visited clinical centers for in-person measurements, including anthropometric measurements. Since then, the WHI has collected comprehensive annual questionnaires on medical history, demographics, and lifestyle characteristics via mail, online surveys and telephone [27].

For [name], we will recruit women who are actively still participating in the WHI and have recently completed an in-home study funded by the WHI. The sample size for [name] is limited to all women who have completed the WHI home visit, as the home visit will provide important information on measured covariates (i.e., body weight, blood-based biomarkers, measures of physical function). The study population is depicted in Fig 1. Cancer survivors will be recruited from a WHI sub-cohort called the Life and Longevity After Cancer (LILAC) study. Postmenopausal women with no cancer history (“non-cancer controls”) will be recruited from a WHI sub-cohort called the Long Life Study 2 (LLS2), a minority enriched sub-cohort of women [28, 29]. The WHI is currently completing in-home study visits for LILAC and LLS2 participants. Home visits consist of anthropometric measures (e.g., height, weight, blood pressure), assessment of physical function via the short physical performance battery (SPPB), and a fasting venous blood draw [30].

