### [name] study overview

All contact for the [name] study will occur remotely, via telephone and mail, after the WHI home visit has been completed for both LILAC and LLS2 participants [28, 29]. Data collection for [name] (D_3_Cr muscle mass) is currently underway and scheduled to be completed by 2025. We will measure D_3_Cr muscle mass at one time point shortly after completion of the WHI home visits. Annual WHI questionnaires will assess self-reported functional outcomes over time, including ability to complete activities of daily, disability, and mobility limitation, enabling examination of muscle mass as a predictor of these longitudinal outcomes.

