#### Statistical plan

*Aim 1*. We will create age-standardized muscle mass percentile curves to characterize the distribution of D_3_Cr muscle mass in cancer survivors and non-cancer controls. We hypothesize that cancer survivors will have lower muscle mass compared to age-matched cancer-free controls. We will also develop percentile curves for women from different racial/ethnic minority groups to examine potential differences in the distribution of muscle mass among Non-Hispanic White, Non-Hispanic Black, and Hispanic women. Additionally, to examine the effect of cancer-related variables on age-standardized muscle mass among cancer survivors, we will create percentile curves stratified by time since diagnosis and treatment modality (chemotherapy yes/no). These stratified analyses will specifically address questions regarding the effect of heterogeneity of cancer type and stage of cancer at diagnosis. According to guidance from the World Health Organization and U.S. Centers for Disease control, precision of estimates for growth curves depend on the number of participants at given percentile value [35–37]. The World Health Organization suggests adequate precision for growth curve modeling is achieved with a minimum of sample size of 200 participants per percentile [35]. Based on the planned recruitment of WHI participants, we will have adequate power for this analysis.

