*Aim 2*. To examine the association between D_3_Cr muscle mass and functional outcomes in cancer survivors and non-cancer controls, we will use data on physical performance (SPPB) and muscular strength (grip strength) from the WHI home visits. We hypothesize that cancer survivors will have worse physical function than non-cancer controls and will also experience greater decline in physical function over time. We will first investigate the cross-sectional joint distribution of D_3_Cr muscle mass, muscle strength, and physical function for cancer survivors and non-cancer controls. Muscle strength will be measured using handheld dynamometer (Jamar hand dynamometer; Lafayette Instruments, Lafayette, IN). Participants are instructed to squeeze the handle of the dynamometer as hard as possible for two trials per hand. Physical function is being measured via the Short Physical Performance Battery (SPPB), a validated test of physical function consisting of three tests: balance, gait speed, and chair stands. Short physical performance battery scores range from 0 to 12, with higher scores indicating better physical function. Multivariate adjusted linear regression models will be used to calculate means and 95% confidence intervals of muscle mass by SPPB score (0–12), timed walk (meters/second), number of chair stands, and grip strength (kg). These models will include a product interaction term (muscle mass x cancer survivorship status) to separately estimate these relationships among cancer survivors and non-cancer controls [38–40]. Among cancer survivors, we will examine effect heterogeneity by time since diagnosis, cancer site, and treatment modality by including product interaction terms in our fully adjusted regression models (i.e., to control for potential confounding by health or lifestyle related characteristics).

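### Aim 1 muscle curves by time since diagnosis compare women selected on different lengths of survival, so they can show a spurious upward gradient or mask continuing loss

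*Protocol article*

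**What the plan says.** The Aim 1 paragraph of the Statistical plan adds a within-survivor analysis: "we will create percentile curves stratified by time since diagnosis and treatment modality (chemotherapy yes/no"). Its purpose is given as "to examine the effect of cancer-related variables on age-standardized muscle mass among cancer survivors". The paragraph then says that these stratified analyses deal with heterogeneity of cancer type and stage at diagnosis. Neither of the two named stratifiers is type or stage.

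Three other statements set the context:
- Study overview: "We will measure D_3_Cr muscle mass at one time point shortly after completion of the WHI home visits". No woman contributes a change in muscle mass.
- Study population: "we will recruit women who are actively still participating in the WHI and have recently completed an in-home study funded by the WHI". The survivors are a prevalent sample. According to the LILAC section, the sites being recruited are breast, lung, colorectal and endometrial.
- Background: "There is compelling evidence that muscle quantity and function increases morbidity and mortality after a diagnosis of cancer". Read literally, the direction is reversed. The rest of that paragraph makes clear that low muscle is the adverse state.

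**The concern.** Take two women of the same age at the muscle test, one diagnosed 2 years ago and one 20 years ago. The second is in the sample only because she lived through 20 years of cancer-related risk. If low muscle raises that risk, as the Background holds, the 20-year stratum has lost more of its low-muscle women than the 2-year stratum. Age-standardisation does not remove this, because the selection acts through time since diagnosis at a given age.

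The strata are given an effect interpretation, and with one measurement per woman nothing in the data can separate a change within women from a change in who is left. The Background names longer-term change in muscle mass among survivors as a gap in knowledge, so a rising or flat gradient invites interpretation. The lower tail is at stake as well as the mean, because Aim 3 defines low muscle mass as below the 10th percentile for age.

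**Working it through.** The plan states no figure on this point, so there is none to reproduce. The check asks how large a gradient selection alone can produce when muscle does not change at all.

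**Inputs from the documents.** One muscle measurement per woman; entry conditional on being alive and active; a link between muscle and death after cancer, without a hazard ratio; low muscle at diagnosis in 30% of breast and 42% of colorectal patients.

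**Assumed, not in the documents.** The hazard ratio (HR) per SD lower muscle; the excess mortality d that separates a long-time from a short-time stratum; the yearly excess hazard h; a muscle rank that stays the same from diagnosis to test.

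**Model 1.** Let z be the age-standardised muscle score, z ~ N(0,1). Survival of the excess risk is S(z) = exp(−H·HR^(−z)). H is solved so that the average of S(z) over z equals 1 − d. The mean shift is the average of z weighted by S(z). At HR 1.4, H is 0.100, 0.214, 0.498 and 0.913 for d of 10%, 20%, 40% and 60%.

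| HR per SD | d = 10% | d = 20% | d = 40% | d = 60% |
|---|---|---|---|---|
| 1.2, mean shift (SD) | 0.02 | 0.04 | 0.09 | 0.16 |
| 1.4, mean shift (SD) | 0.04 | 0.07 | 0.17 | 0.29 |
| 1.6, mean shift (SD) | 0.05 | 0.10 | 0.23 | 0.39 |
| 1.4, 10th percentile shift (SD) | 0.04 | 0.09 | 0.20 | 0.35 |

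At HR 1.4 and d = 60%, only 4.9% of the remaining women lie below the original 10th percentile.

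**Model 2.** The excess hazard is h·HR^(−z) per year, and the stratum at 20 years is compared with the stratum at 2 years.

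| h per year | HR per SD | Mean shift, hazard lasting | Mean shift, hazard ending at 10 years |
|---|---|---|---|
| 0.01 | 1.2 | +0.03 SD | +0.015 SD |
| 0.03 | 1.2 | +0.10 SD | +0.04 SD |
| 0.03 | 1.5 | +0.21 SD | +0.10 SD |
| 0.05 | 1.5 | +0.33 SD | +0.16 SD |

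At HR 1.0 the shift is zero, so the gradient comes from the link between muscle and death and from nothing else in the model.

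**Model 3.** Two groups, starting from the 30% low-muscle prevalence in the Background. The share with low muscle at time t is 0.30·exp(−h·HR·t) / [0.30·exp(−h·HR·t) + 0.70·exp(−h·t)]. Here HR compares low with not-low muscle.
- HR 1.2, h 0.02, t = 20: 0.1856 / (0.1856 + 0.4692) = 28.3%, against 29.8% at 2 years.
- HR 1.6, h 0.05, t = 20: 0.0606 / (0.0606 + 0.2575) = 19.0%, against 28.8% at 2 years.

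**Changing rank.** If the muscle score that drove survival correlates r with the score measured later, the mean shift is multiplied by r. With an assumed r of 0.5, the 0.17 SD above becomes 0.5 × 0.167 = 0.08 SD.

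**The case against.** A reader might infer that selective death will appear as muscle recovery, and that this undermines the study's central question. The documents do not support that. Nowhere does the article say that the time strata will be read as recovery. The stratification is an addition to Aim 1; the main objectives concern survivors against controls, and prediction. True long-term loss could outweigh the artefact and leave a flat or falling gradient. Stage mix, age at diagnosis and treatment era can push either way. The home-visit requirement may also exclude recently diagnosed women who are ill, which would raise the short-time stratum.

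The size is also open. The hazard ratio, the mortality, the site mix and the stratum cut-points are not given, and the larger shifts need 40% to 60% excess mortality and a stable muscle rank. In addition, since "participants have been active participants in the WHI study since the 1990s", ordinary mortality selection at a given age is largely shared across strata. Only the cancer-related part differs.

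A reader might extend the point to Aim 2, where "we will examine effect heterogeneity by time since diagnosis, cancer site, and treatment modality". That does not follow. The interaction there concerns the slope of the relation between muscle and function, and a shift in the mean of muscle does not by itself bias a slope.

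These objections limit the certainty and the scope. They do not remove the problem. For describing women alive today the unweighted curves are sound, but the plan asks them to show an effect. The LILAC section says that analyses by site or stage are possible, yet the Aim 1 text names neither as a stratifier. The potential problems listed in the Discussion cover non-response, loss to follow-up and sample return, and do not mention survival to the muscle test.

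**Conclusion.** The concern holds in a limited form. Followed as written, the Aim 1 strata by time since diagnosis can produce a spurious upward gradient or mask continuing loss. The direction of the artefact follows from the protocol's own premise about muscle and mortality. Its size is not known from the documents: under the assumed ranges it goes from negligible (about 0.02 SD) to material (about 0.3 SD, and 0.39 SD in the most extreme combination), and it shrinks in proportion if muscle rank changes after diagnosis. The net observed gradient could still be flat or falling. Separately, the statement that strata by time and chemotherapy address type and stage is not correct as it stands, because neither stratifier separates them.

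**What to change.** In the Aim 1 paragraph of the Statistical plan:

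1. Make the time-since-diagnosis comparison within cancer site and stage, or adjusted for both. Where cells are small, pool categories or compare model-based z-scores in place of separate curves. LILAC already records site and stage.
2. Correct the sentence that credits the time and chemotherapy strata with addressing type and stage.
3. State that these curves describe current survivors and do not estimate change in muscle after cancer.
4. As a sensitivity analysis only, weight by the inverse probability of surviving and taking part from diagnosis to the muscle test. Estimate it in all WHI women diagnosed with these four cancers, dead or alive.

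Items 2 and 3 cost a sentence each. Item 1 gives smaller cells and wider intervals, and fine splits may fall short of the minimum of 200 participants per percentile that the article cites. Item 4 needs one survival and participation model and one extra set of curves. It corrects only for measured predictors. D3-creatine muscle mass before diagnosis was not measured, so part of the selection will remain, which is why the weighted result should not replace the main one.

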### LILAC (Life and Longevity After Cancer) cohort

LILAC is a cohort of cancer survivors embedded within the WHI. Recruitment protocols for LILAC include: WHI participants who initially self-report a cancer diagnosis and self-report is confirmed by review of medical records by trained physician adjudicators. All data is coded using NCI SEER (Surveillance, Epidemiology, and End Results) standards [28]. LILAC participants who are survivors of breast, lung, colorectal, or endometrial cancer are currently being recruited for home visits.

Information on cancer type, tumor characteristics (e.g., molecular testing, stage and grade), cancer treatments and outcomes are collected as part of LILAC. Medical records are reviewed by trained physician adjudicators to confirm the previously documented diagnostic information and records information on surgery type and date(s); tumor characteristics (HER2, estrogen receptor status); types and start dates of neoadjuvant and adjuvant chemotherapy; radiotherapy along with total dose; biologic therapies; and hormonal/endocrine therapies and enters these directly into the WHI extension study database. For WHI participants enrolled in fee-for-service Medicare at the time of their cancer diagnosis, WHI obtains treatment and recurrence through Medicare linkage. For participants with cancer who were not covered by fee-for-service Medicare at time of diagnosis, WHI collects medical records to obtain comparable data. In addition, LILAC surveys collect self-reported information on initial cancer treatment including surgery type, chemotherapy, hormonal therapy, radiation therapy, biological therapies and complementary/alternative medicine, including type, start dates, and providers of these treatments; new cancer events related to their primary cancer diagnosis; longer-term disabling conditions; effects on quality-of-life that are common sequelae to many cancers or their treatments but not covered by WHI questionnaires (e.g., lymphedema, cardiotoxicity, nephrotoxicity, neurotoxicity); and questions on insurance coverage, income, employment status, access to care, recurrence and health outcomes such as anxiety, depression, overall quality of life, and self-rating of health [31–34]. These rich data will allow us to fully characterize and control for heterogeneity by cancer site and severity, enabling meaningful analyses both overall and when stratified by cancer site or stage.

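### Aim 1 claims that its survivor curves address cancer type and stage, but they are stratified only by time since diagnosis and chemotherapy

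*Protocol article*

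**What the plan says.** The Statistical plan, Aim 1, sets out an additional analysis among survivors. Its purpose is "to examine the effect of cancer-related variables on age-standardized muscle mass among cancer survivors", and its form is "percentile curves stratified by time since diagnosis and treatment modality (chemotherapy yes/no"). The sentence that follows says what these curves will deliver: "These stratified analyses will specifically address questions regarding the effect of heterogeneity of cancer type and stage of cancer at diagnosis".

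Three other places bear on the point.

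- The LILAC cohort section lists the sites: "LILAC participants who are survivors of breast, lung, colorectal, or endometrial cancer are currently being recruited for home visits". It also confirms that the variables exist: "Information on cancer type, tumor characteristics (e.g., molecular testing, stage and grade), cancer treatments and outcomes are collected as part of LILAC".
- The same section says in general terms that the data are rich enough for control of heterogeneity, "enabling meaningful analyses both overall and when stratified by cancer site or stage". It does not tie this to an aim.
- Aim 2 plans product interaction terms for "effect heterogeneity by time since diagnosis, cancer site, and treatment modality" in the models that relate muscle mass to physical function.

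**The concern.** The sentence about type and stage points back to the curves just described, and those curves contain neither factor. A chemotherapy-yes curve combines breast, lung, colorectal and endometrial survivors at every stage, and so does a chemotherapy-no curve. Placing the two side by side cannot show how muscle mass differs by site or by stage.

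Two things are at stake. First, a later report could cite the protocol as having prespecified a treatment of type and stage that the stated curves do not provide. Second, Aim 1 describes the purpose of these curves in terms of an effect. If chemotherapy use varies with site and stage, and muscle mass does too, then some of the gap between the chemotherapy curves reflects which cancers were treated and not the treatment. Age standardisation does not remove that.

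**Working it through.** The plan gives no figure to reproduce here. The main check is a comparison of texts; the arithmetic serves only to size the confounding.

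**Step 1: what Aim 1 uses against what it claims.**

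| Factor | Survivor stratum in Aim 1 | Said to be addressed by those strata |
|---|---|---|
| Time since diagnosis | yes | – |
| Chemotherapy yes/no | yes | – |
| Cancer type | no | yes |
| Stage at diagnosis | no | yes |

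No covariate is named for the curves apart from the age standardisation. The two lists do not overlap.

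**Step 2: does another section fill the gap?**

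- The LILAC section says what the data make possible. It defines no Aim 1 curve by site or stage.
- The Aim 2 interactions include site but not stage. They ask whether the link between muscle mass and function varies among survivors. Aim 1 asks how muscle mass itself is distributed.
- The longitudinal model in Aim 2 is to be adjusted for cancer-related confounders that are not itemised. Stage may be among them, but that model has functional status as its outcome.

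None of these supplies an Aim 1 analysis by type or stage.

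**Step 3: how large could the case-mix difference be?** Suppose that chemotherapy has no effect and that advanced stage lowers mean muscle mass by *d* SD. Let *p1* and *p0* be the shares with advanced stage among treated and untreated survivors. The stratum means are μ − *d*·*p1* and μ − *d*·*p0*, so the apparent chemotherapy difference is

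*d* × (*p1* − *p0*).

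The same formula serves for a site contrast. The article gives none of *d*, *p1* or *p0*, so all the values below are assumptions.

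| *d* (SD) | 50% vs 50% | 60% vs 30% | 70% vs 20% | 80% vs 10% |
|---|---|---|---|---|
| 0.1 | 0 | 0.03 | 0.05 | 0.07 |
| 0.2 | 0 | 0.06 | 0.10 | 0.14 |
| 0.3 | 0 | 0.09 | 0.15 | 0.21 |

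For example, 0.3 × (0.80 − 0.10) = 0.21 SD and 0.1 × (0.60 − 0.30) = 0.03 SD. With equal shares the difference is 0 whatever the value of *d*.

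**The case against.** The strongest reply is that this is a drafting slip. The LILAC section shows that the authors have stratification by site and stage in mind, and those strata may have dropped out of the Aim 1 list when the plan was condensed. Percentile curves are also a descriptive tool, for which unadjusted strata are normal, and the affected text is an extra display among survivors only. The survivor–control comparison, the Aim 2 longitudinal model and the Aim 3 prediction models do not depend on it, and no data would be lost.

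Much of this stands, and it limits how serious the point is. It does not rescue the sentence. The article names its strata and then makes a specific claim about those same strata. A fuller plan could add analyses, but it could not make these two factors stand for type and stage. If chemotherapy is meant as a proxy for them, its curves cannot also be read as showing treatment.

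A reader might infer three stronger things that the document does not support:

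- **Stage is used nowhere in the study.** The unspecified cancer-related confounders in Aim 2 may include it. What can be said is that stage is named neither as an Aim 1 stratum nor as an Aim 2 interaction factor.
- **Cancer type goes unexamined throughout.** Aim 2 examines heterogeneity by site. The gap is in Aim 1.
- **The chemotherapy curves are in fact confounded, perhaps entirely.** The article reports neither chemotherapy use by site or stage nor any association of stage with muscle mass. The curves are open to confounding; whether and how far they are confounded is unknown.

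**Conclusion.** The point holds for Aim 1 and should be fixed. That the claim about type and stage is false as written follows from two adjacent sentences and needs no assumption.

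The confounding part is an inference. It rests on the pooling of four sites and all stages, on age being the only stated standardisation, and on the word effect in the stated purpose. Over the assumed grid, case mix alone would produce a difference of 0 to 0.21 SD; the true figure could lie outside that range. The weight of the point does not come from this range: Aim 1 promises a conclusion that its strata cannot give.

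**What to change.** 1. Among survivors, add cancer site and stage at diagnosis to Aim 1 in one of two ways:
   - as further strata, where the precision criterion that Aim 1 itself cites (at least 200 participants per percentile) is met. The article gives no stratum counts, so this has to be checked against actual recruitment;
   - or by regressing the age-standardised muscle-mass z-score (z-scores are already planned in the abstract) jointly on site, stage, time since diagnosis and chemotherapy, and reporting mutually adjusted differences with 95% confidence intervals. The z-scores must come from one common reference; standardising within strata would remove the differences of interest.
2. Label the chemotherapy and time-since-diagnosis curves as descriptive.
3. Correct the sentence on type and stage to point to the new analysis, or delete it.

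The cost is one extra analysis on variables that LILAC already collects, plus wording. Sparse combinations of site and stage will give wide intervals, and some strata may be too small for a curve. The regression compares means and not percentiles, so it supplements the curves and does not replace them. If the authors want neither addition, deleting the sentence and labelling the curves as descriptive removes the false claim, but leaves type and stage unexamined in Aim 1.

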**Methods:**

This study protocol describes the use of a novel method of muscle mass measurement, D3-creatine dilution method (D_3_Cr), in a large sample (n~6000) of community dwelling postmenopausal women from the Women’s Health Initiative (WHI). D_3_Cr will be used to obtain a direct measure of muscle mass remotely. Participants will be drawn from two sub-cohorts embedded within the WHI that have recently completed an in-home visit. Cancer survivors will be drawn from the Life and Longevity After Cancer (LILAC) cohort, and cancer-free controls will be drawn from the WHI Long Life Study 2. The overall objective of this study is to examine the antecedents and consequences of low muscle mass in cancer survivors. The study aims are to: 1) create age-standardized muscle mass percentile curves and z-scores to characterize the distribution of D3- muscle mass in cancer survivors and non-cancer controls, 2) compare muscle mass, physical function, and functional decline in cancer survivors and non- cancer controls, and 3) use machine learning approaches to generate multivariate risk-prediction algorithms to detect low muscle mass.

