Many women experience changes loss of muscle mass as part of the normal aging process [25]. However, there are several key unanswered questions about whether postmenopausal cancer survivors experience greater declines in muscle mass compared to women without a history of cancer. If yes, do they undergo an accelerated aging trajectory, with a different slope and quicker progression to functional impairment and disability? This protocol will describe the design of a prospective longitudinal study using the D_3_Cr method to measure muscle mass in postmenopausal cancer survivors and a comparison group of women without a cancer history (“non-cancer controls”). Both cancer survivors and cancer-free controls are drawn from the same source population, the Women’s Health Initiative (WHI).The specific objectives of this project are to: 1) develop age-standardized percentile curves to characterize the distributions of D_3_- muscle mass in cancer survivors and cancer-free controls, 2) examine whether the associations between muscle mass, physical function, and functional decline differ in cancer survivors and cancer-free controls, and 3) create multivariate risk-prediction algorithms to detect low muscle mass in cancer survivors and cancer-free controls. We hypothesize that cancer survivors will have lower muscle mass and experience accelerated decline in physical function compared to cancer-free controls.

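### Aim 2 hypothesises worse physical function in survivors, but no described model estimates that difference: the cross-sectional contrast is an interaction, and the later survivorship coefficient is conditional on muscle mass

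*Protocol article*

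**What the plan says.** Aim 2 is worded in three places.

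- Abstract, Methods: the aim is to "compare muscle mass, physical function, and functional decline in cancer survivors and non- cancer controls". This is a difference between groups.
- Background, specific objectives: the aim is to "examine whether the associations between muscle mass, physical function, and functional decline differ in cancer survivors and cancer-free controls". This is effect modification.
- Statistical plan, Aim 2: the opening purpose is "To examine the association between D_3_Cr muscle mass and functional outcomes in cancer survivors and non-cancer controls". The hypothesis that follows is again a group difference: "We hypothesize that cancer survivors will have worse physical function than non-cancer controls and will also experience greater decline in physical function over time".

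The same paragraph ties physical function to the SPPB and calls grip a measure of muscle strength. Its first step is to look at the joint distribution of muscle mass, strength and function in each group. The regressions are then to "calculate means and 95% confidence intervals of muscle mass by SPPB score (0–12), timed walk (meters/second), number of chair stands, and grip strength (kg"). On the group contrast it says: "These models will include a product interaction term (muscle mass x cancer survivorship status) to separately estimate these relationships".

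The next paragraph of the Aim 2 plan is longitudinal. The outcome is self-reported activities of daily living from annual questionnaires. The mixed model has a survivorship coefficient, read as the baseline difference after accounting for baseline muscle mass, and a year x survivorship term, read as the difference in slope. A muscle mass x year term will also be examined.

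**The concern.** A group difference in function and a group difference in the muscle-function slope are separate parameters. Survivors can function worse while the slope is the same in both groups, or function equally well on average while the slopes differ. The hypothesis concerns the first parameter and the described cross-sectional models report the second.

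The cross-sectional model is also not coherent as worded. Muscle mass is the quantity whose mean is estimated, and it is also a predictor inside the product term.

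Whether survivors function worse than comparable women is a main question of the study, and the Discussion says the design lets the team separate what is specifically related to cancer. If the text is followed as written, a real deficit in SPPB could go unreported, or a null interaction could be read as evidence against the hypothesis.

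**Working it through.** **Each part of the hypothesis against the contrasts that are described**

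| Contrast described | Outcome | Conditional on muscle mass? | Tests worse function? | Tests greater decline? |
|---|---|---|---|---|
| Muscle mass x survivorship (cross-sectional) | Unclear: muscle mass as worded | Yes | No, it is an interaction | No |
| Survivorship coefficient (mixed model) | Self-reported daily activities | Yes | Not on SPPB, and only net of muscle mass | No |
| Year x survivorship (mixed model) | Self-reported daily activities | Described as after accounting for it | No | Yes |

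No row gives the survivor-control difference in SPPB. Reading the cross-sectional model with function as outcome does not supply it either. The survivorship main effect would then be conditional on muscle mass and, unless muscle mass is centred, would be the difference at a muscle mass of zero.

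**Why conditioning on muscle mass matters here.** Aim 1 and the Background hypothesise lower muscle mass in survivors, and the Discussion reports that pilot data linked muscle mass to physical function. On the article's own premises, muscle mass may lie on the path from cancer to function.

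**Illustration.** The article gives no alpha, effect size, SD or survivor-control split for Aim 2, so there is no figure of its own to reproduce. Only the total of about 6000 (Study population) comes from the document. Assumed: a 1:1 split, two-sided 5%, unit residual SDs, 300 simulated data sets per scenario. With s = survivor:

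- muscle mass: m = −a·s + noise
- function: f = b·m + c·s + d·m·s + noise

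When d = 0, the plain group difference is c − a·b, the muscle-adjusted difference is c, and the interaction is d.

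*Scenario 1: deficit carried wholly by muscle* (a = 0.3, b = 0.5, c = 0, d = 0).

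- Plain difference: 0 − 0.3 × 0.5 = −0.15.
- Standard error: √[(0.5² + 1) × (1/3000 + 1/3000)] = 0.029, so the ratio is 0.15/0.029 ≈ 5.2.

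*Scenario 2: interaction only* (a = 0, b = 0.5, c = 0, d = 0.2).

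| | Plain difference | Muscle-adjusted difference | Interaction |
|---|---|---|---|
| Scenario 1: mean estimate | −0.152 | −0.002 | 0.001 |
| Scenario 1: rejected | 100% | 4.3% | 4.7% |
| Scenario 2: mean estimate | −0.001 | −0.001 | 0.198 |
| Scenario 2: rejected | 3.7% | 5.3% | 100% |

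**Range.** The part of the deficit removed by adjustment is a·b. With b = 0.5 it is 0.05, 0.10 and 0.15 for a = 0.1, 0.2 and 0.3. Divided by the within-group SD, √1.25 = 1.118, these are 0.045, 0.089 and 0.134 SD. The smallest plain difference detectable with 80% power among 6000 women is (1.960 + 0.842) × √(1/n₁ + 1/n₂), which gives 0.072 SD at a 50:50 split, 0.079 at 30:70 and 0.090 at 20:80. The 0.134 SD case is therefore detectable at any of these splits. The 0.089 SD case is detectable at the first two and borderline at 20:80. The 0.045 SD case falls below the 80% power threshold at all three.

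**The case against.** The strongest reply has four parts.

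1. **The decline half of the hypothesis has a test.** The year x survivorship term is named and interpreted. This stands. A reader might infer that Aim 2 has no deciding comparison at all, and the article does not support that. The gap is in the cross-sectional half.

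2. **Function is described by group.** The joint-distribution step will show SPPB in survivors and in controls. This stands as far as it goes, but the step names no contrast, adjustment or interval, so it does not test the hypothesis.

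3. **The intended model probably has function as the outcome.** The opening purpose and the product term both point that way, and such a model would ordinarily carry a survivorship term. That is plausible, but the sentence on means of muscle mass points the other way, so the text needs correcting. On the favourable reading the survivorship term is still conditional on muscle mass.

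4. **The Abstract and Background wordings are compatible parts of one aim.** They can be, if stated as two questions. The article does not do this, and it attaches a hypothesis about one question to models for the other.

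A reader might also infer that SPPB, timed walk, chair stands and grip compete to decide the aim, with an inflated false-positive rate. The article does not support this. It ties physical function to the SPPB, labels grip as strength, and lists gait speed and chair stands among the SPPB's own tests. It states no alpha and no rule by which any one measure would settle the aim. Formal ranking of outcomes is also something a condensed article may leave to the full plan.

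**Conclusion.** The point holds for the cross-sectional half of the hypothesis. The article words Aim 2 as two different questions, hypothesises worse physical function in survivors, and describes no model that estimates that difference in SPPB. The only stated cross-sectional group contrast is an interaction, from a model in which muscle mass is both outcome and predictor. The mixed-model survivorship coefficient does not fill the gap, because it concerns self-reported daily activities and is net of muscle mass.

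The mismatch is in the text and needs no assumption. Its size does. If muscle mass carries the whole deficit, both the adjusted coefficient and the interaction reject at about the nominal 5% while a plain difference of 0.15 is found in every run. If muscle mass carries only part, only that part is lost. The effect sizes, split and significance level are assumptions. The simulation shows that the contrasts can disagree in this design, not that they will.

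**What to change.** - **State two questions.** In the Abstract, the Background objectives and the Aim 2 plan, list separately (i) the survivor-control difference in function and decline and (ii) whether the muscle-function association differs by survivorship.
- **Correct the cross-sectional model.** Make the function measure the outcome, with muscle mass, survivorship and their product as predictors. This answers question (ii).
- **Add the missing model.** Fit a confounder-adjusted linear regression with SPPB total as outcome and survivorship as the tested term, without muscle mass, and report the difference with a 95% CI. Name it as the test of worse physical function.
- **Keep year x survivorship as the test of greater decline.** Report it from a model without the muscle mass terms as well as with them. The muscle mass x year term matters most here, since it can absorb a slope difference that runs through muscle.

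The cost is wording and one or two extra regressions on SPPB and questionnaire data that the study already plans to use. The small downside is that the interaction results can no longer stand in for the group-difference hypothesis.
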